### Validity and reliability

To ensure data quality, we will hold regular appointments to discuss the process of data collection and problems during its process. We have developed a data collection manual with detailed explanation of every question in the assessments and phrasings that should explicitly not be used, because they could compromise the assessment. No external data audit is planned.

Regarding the intervention, the coordinators of the APNs will supervise them and also hold regular meetings to ensure process quality of the intervention and help in dissolving barriers. Especially in the beginning phase of the intervention, problems will inevitably come up. Since the APNs are all beginners in their new role, we believe some guidance is warranted.

### Ethics and dissemination

We do not expect any adverse health outcomes during this study, which are directly related to the intervention. Possibly, participants might feel stressed by the intervention and data collection. Therefore, we evaluate ongoing consent at every personal contact with the study or practice team. We will seek consultation with the primary caregivers in case we have the impression that something is awry, e.g., the participant does not want to participate anymore, but is too polite or hesitant to voice his feelings. Consequently, criteria for discontinuing the intervention are participants’ request or worsening of condition. We will further document reasons for dropping out of the study and inspect every case individually for relation to any harms. Additionally, the APNs are encouraged to report any adverse outcomes or errors related to their practice. After each case, the project lead will decide upon a continuation of the study. Since there is no anticipated harm, there is no compensation for trial participation.

There will be no formal data monitoring committee; however, we will present our data at the bi-yearly meetings of the project advisory board, which comprises of independent experts.

All physical data will be stored in a lockable cabinet in a lockable office. The consent forms will be archived separately. The electronic data will be stored in a password protected folder. Only the study personnel has access to this folder. The reference list with pseudonyms and plain names is stored separately by the person performing the randomization at BUAS.

The findings will be disseminated in peer-reviewed journals and presented at national and international conferences relevant to the subject fields.

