### Design

The study design is a randomized-controlled trial (RCT) with waiting list and superiority framework. People being in the control group (CG) will receive the intervention after completion of data collection after 12 months. It will be conducted from January 2022 to December 2024. The study is accompanied by a mixed-methods process evaluation consisting of quantitative structured interviews as well as qualitative interviews focusing on the process as well as experiences of different stakeholders (APNs, clients, caregivers, care providers in the community) as well as an inclusive research group. In the latter, people with intellectual disabilities will act as co-researchers and conceptualize their own part in the evaluation. We will report on the RCT only, because the conceptualization is finalized. The flow of participants and data collection is shown in Table 1.

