The CG will receive usual care. The topic of prevention and health promotion is not well covered by the existing practice and therefore we opted not to offer an active intervention. The APNs will not initiate any interaction with participants from the CG. However, because the APNs are situated right within the seven districts in offices open to the public, it cannot be excluded that control patients could receive advice or counseling on healthcare problems.

To improve adherence to the intervention, detailed intervention descriptions were developed for each home visit. However, due to the nature of this communicative, educational, coordinating complex intervention, a degree of flexibility is needed to tailor the intervention to the needs of individuals in this diverse population.

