Data collection for outcome evaluation is planned as face-to-face interviews based on a questionnaire consisting of the aforementioned outcome measures as well as date of birth and data collection, sex, living situation, support through formal or informal care, and the rater’s assessment of the potential study group assignment of the participants including justification to check the blinding procedure. Data collection will be conducted in the participants’ homes or a place of their choice. This can be, for example, their own flat, a residential living group, or a residential facility. A primary caregiver (legal representative, family member or professional caregiver) is going to be present for the evaluation of the health status as well as the quality of life. This usually has the beneficial side effect that many participants feel more comfortable with their caregivers present and they can help them in clarifying questions, because they are familiar with their context, e.g., if you want to know whether the person is able to walk one kilometer the concept of 1 km is sometimes difficult to grasp. It is easier, if a caregiver can give an example of something that is as far away, e.g., a supermarket.

Data collection for the process evaluation is also planned as face-to-face interviews and is directed towards the clients as well as their primary caregivers. The questionnaire comprises of questions on the number of contacts, quality of communication between the APN and clients and caregivers, quality of collaboration, the professional relationship, satisfaction with the intervention, if new knowledge has been gained through the intervention on stress, mobility, nutrition, and addiction, and finally potential for improvement of the intervention. In our previous study on medication management of people with intellectual disabilities, it has proven useful to first ask dichotomous questions, e.g., “were you satisfied with the caregivers?” and then to ask on an ordinal scale how (un-)satisfied they were. We will employ this approach throughout the questionnaire.

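### Apart from the review of dropouts, adverse outcomes are actively reported only by the nurses treating the intervention group, so harms in participants who stay are ascertained differently by arm

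*Protocol article*

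**What the plan says.** Ethics and dissemination expects no adverse health outcome directly caused by the intervention and names stress from the intervention or the interviews as possible. It then describes three routes by which a harm could come to light:

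- A consent and distress check in both arms: "Therefore, we evaluate ongoing consent at every personal contact with the study or practice team". The primary caregiver is consulted if something seems wrong.
- A review of dropouts, not limited to one arm: "We will further document reasons for dropping out of the study and inspect every case individually for relation to any harms".
- As an addition to these, nurse reporting: "the APNs are encouraged to report any adverse outcomes or errors related to their practice".

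The project lead decides on continuing the study after each case. There is no formal data monitoring committee.

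On contact with controls, the section Intervention states: "The APNs will not initiate any interaction with participants from the CG". It allows for chance contact at the nurses' public offices: "it cannot be excluded that control patients could receive advice or counseling on healthcare problems". Under Design, controls "will receive the intervention after completion of data collection after 12 months".

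Under Outcomes and data collection, raters interview both groups at t0, t1 and t2. The questionnaire holds the outcome measures, dates, sex, living situation, support and the rater's guess of allocation. "A primary caregiver (legal representative, family member or professional caregiver) is going to be present for the evaluation of the health status", and also for quality of life.

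**The concern.** A fair comparison of harms needs the same question, asked in the same way and equally often, in both arms. Here the one active report depends on a nurse noticing an event, judging it related to her own work and choosing to report it. That nurse has planned contact with one arm only during the randomized comparison. The raters see both arms and are blinded, but the article gives them nothing to record on adverse events.

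At stake is what the final report may say about safety. More reports from the intervention group could reflect only who was watched. Few or no reports could reflect only the voluntary, practice-related filter. Neither result would confirm or refute the expectation of no intervention-related harm.

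**Working it through.** The article gives no figure on this point, so there is none to reproduce. The check is to follow each route for a participant who stays in the trial to month 12.

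| Route | Intervention group | Control group | Records an event in someone who stays? |
|---|---|---|---|
| APN report | Yes, voluntary, if related to practice | No planned contact; chance office contact only | Intervention group: possibly. Controls: only by chance |
| Dropout review | Yes | Yes | No, it covers leavers only |
| Consent and distress check | Yes, study and practice team | Yes, study team | None described; it concerns willingness and distress |
| Rater questionnaire, t0 to t2 | Yes | Yes | No adverse-event item listed |
| Process evaluation | t3, month 13 | t4 and t5, months 18 and 24 | No adverse-event item listed, and not parallel in time |

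**Reach of the dropout review.** Inputs from Data processing and analysis: 256 planned participants and 30% assumed dropout. Expected to stay: 256 × (1 − 0.30) = 179.2, about 179. For these, a hospital admission or an injurious fall would not be picked up by this route.

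**Opportunity for the consent check.** Planned face-to-face contacts up to one year:
- Controls: t0, t1 and t2 = 3.
- Intervention group: the same 3 plus 4 home visits = 7, with further liaison and a review of the prevention plan every two months.

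So even the route that covers both arms is applied more often in one of them.

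**Result.** For participants who stay, the only row that can produce a recorded adverse outcome is the first, and it works differently by arm by design.

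**The case against.** The case on the other side has five parts.

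1. The APN report supplements other routes. The dropout review and the consent check both cover controls, and the consent check addresses the one harm the authors foresee, stress. This stands, and it rules out a stronger reading. A reader might infer that harms are reported by the APNs alone and can be counted in one arm only, with a certain zero among controls. The article does not support that: leavers in both arms are reviewed, and the article itself allows for chance contact between controls and APNs.
2. The article plans no between-arm comparison of harms, and continuation is decided case by case, not on a rate. This also stands. The point is therefore about what the reports can be used for. It does not show that a planned analysis is wrong.
3. General decline would show in WHODAS 2.0 and EQ5D-VAS, rated blind in both arms. That is true, but these are scores and do not count events.
4. A reader might want to size the distortion by applying an assumed event rate to 128 per group and setting the result against zero. This does not follow from the plan. The restriction to practice-related outcomes would exclude most background events, and controls are not a guaranteed zero.
5. The article condenses a full protocol that is not shown, and the health economic evaluation is expressly left out. Either could hold a both-arm event record. This limits certainty. It does not remove the finding, because the article states an ascertainment rule that treats the arms differently and does not merely omit detail.

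**Conclusion.** The point holds in this limited form. For participants who stay, the article's only active adverse-outcome reporting is voluntary, filtered by relation to the nurses' own practice, and tied to staff with no planned contact with controls before the 12-month data are complete. The two both-arm routes do not close the gap, because one covers only leavers and the other has no described record of events. The resulting reports can describe problems in delivering the intervention. They cannot support a statement that harms were more, less or equally frequent with it.

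No size can be given for the distortion. The net effect on any count is also uncertain, since extra contact raises detection in the intervention group while the voluntary, practice-related filter lowers it. The primary and secondary efficacy analyses are not affected.

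The conclusion assumes that the questionnaire content in the article is complete and that neither the full protocol nor the economic data collection already records events in both arms.

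**What to change.** - At t1 and t2, have the blinded raters ask participant and caregiver in both groups the same short list of events since the last interview, for example unplanned hospital admission, injurious fall and marked distress. Do not ask about cause.
- Ask these items last, after the outcome measures are complete.
- Take deaths from the dropout documentation. Where the health economic data already record admissions in both arms, use those instead of a new question.
- Report these events by arm. Keep the APN reports as a separate description of practice-related events in the intervention group, and state that they are not used for comparison between arms.

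The cost is a few questions in interviews that already take place, an entry in the data collection manual, and an amendment by the route the article describes. Interviews become slightly longer. There is a small added risk that an answer reveals the allocation. Asking last protects the scores of that visit, but a rater unblinded at t1 could carry this to t2 if the same rater returns.

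On timing, the first participant was recruited on 1 September 2022, so t1 interviews fell due from about March 2023, just after publication on 23 February 2023. If the interviews are already over, the remaining step is to report APN-reported events for the intervention group alone and to say that the trial gives no between-arm evidence on harms in participants who stayed.

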### Roles and responsibilities

This is an investigator-sponsored study. Hamburg University of Applied Sciences (HUAS) is the primary sponsor with project lead [name]. [name]: [contact]. The primary sponsor is part of the study team as consortium lead and therefore responsible for the coordination and management of the project. Recruitment of participants is the responsibility of the ESA with support by HUAS. Data collection and analysis will be performed at the BUAS. The economic analysis is carried out by the German Hospital Institute. Intervention delivery is carried out by the ESA. An independent advisory board consisting of experts from science, politics, professional practice, and the target group is going to oversee the project in two meetings each year.

### Plans for communicating important protocol amendments to relevant parties

Any modifications to the protocol that could affect the conduct of the study and the potential benefit to participants or affect participant safety, including changes in study objectives, study design, population, sample size, study procedures, or significant administrative aspects, will require a formal amendment to the protocol. We will report important changes to the protocol to the funder and need its approval as well as that of the ethics committee. In addition, the details in the German Clinical Trials Register will be revised accordingly.

## Discussion

Germany is significantly behind regarding international developments of nursing care especially in ANP. Here, distortions in the execution of the intervention may occur. For example, it will be a challenge to operate in the field of prevention and health promotion in Germany. There are a lot of barriers with regard to interprofessional collaboration due to the not well-known field of ANP. They need to show determination and perseverance to influence existing structures. Additionally, in many cases, the APNs will have to exercise a lot of advocacy to get people into existing programs.

The COVID-19 pandemic could interfere with the trial process. If there is another peak of the pandemic in late fall or winter, it could be difficult to carry out both home visits and data collection, especially for people living in institutions. Appropriate digital fallback options will be provided for this.

### Limitations

This study is only performed in the city of Hamburg. Therefore, we cannot exclude that especially in the more rural areas of Germany the intervention might be more difficult to perform. However, we believe that it should also work in other areas than Hamburg, since there might be even more need for case management and nursing expertise, because there is less availability of healthcare professionals in general.

Due to prior experiences with recruitment, we did not opt for a cluster-randomized trial. It is quite difficult to recruit a sufficient number of participants from one, e.g., institution to fill suitable clusters. Therefore, we cannot exclude possible effects of the institution on the outcomes. As mentioned before, there are no suitable assessments for health literacy for this specific topic and population and therefore we opted not to measure it with an objective outcome measure. We will measure elements of knowledge via the process evaluation in the waiting group, though.

### Trial status

This is protocol version 1.4. The first participant was recruited on 1 September 2022. Recruitment will be concluded in January 2023. The study will be completed in December 2024.

## Data Availability

The datasets analyzed during the current study and statistical codes will be available from the corresponding author on reasonable request, as is the full protocol.

## Abbreviations

ANCOVA: Analysis of covariance
ANP: Advanced nursing practice
APN: Advanced practice nurse
BUAS: Bielefeld University of Applied Sciences
CG: Control group
ESA: Evangelische Stiftung Alsterdorf
HUAS: Hamburg University of Applied Sciences
IG: Intervention group
RCT: Randomized-controlled trial
